## Discussion

### Expected Findings

Our review of the literature (summarized in Multimedia Appendix 1) demonstrated that all published guidelines by non-neurosurgical societies are largely inconsistent. While some suggest against the use of pharmacological prophylaxis in the majority of patients undergoing neurosurgery, others suggest stratifying patients based on risk of VTE, including those with malignancy or immobilization, and providing pharmacological prophylaxis in the high-risk group. Moreover, the choice of anticoagulant is different between published guidelines, and most do not consider weight-based dosing.

In devising our protocol, we borrowed heavily from the trauma and neurocritical care literature when choosing the timing, agents, and dosing for VTE cPpx. NASS working group on VTE prophylaxis [9] notes that the safety and utility of cPpx is controversial, and the literature does not support a specific perioperative start time point nor duration of cPpx. However, the working group acknowledges that LMWH initiated on the day of surgery may be safe for patients undergoing elective spine surgery and makes a consensus-based recommendation for it in their 2009 guidelines [9]. On the other hand, the ACCP recommends initiating cPpx in trauma neurosurgical patients within 24-72 hours of admission pending a stability scan [7]. The NCC guidelines [36] alternatively note that VTE cPpx should be initiated after 24 hours of admission for patients with aneurysmal subarachnoid hemorrhage, after 48 hours for patients with intracerebral hemorrhage, and within 24-72 hours for patients with TBI, but not before. We have elected to initiate cPpx for all admitted patients on the neurosurgery service within 24-48 hours of scheduled surgery. Patients who have a contraindication to anticoagulation or are at a high risk of intracranial bleeding will enter the protocol pending a stable head computed tomography.

In terms of the choice of agent for VTE cPpx, Nyquist et al [36] recommend prophylaxis with UFH for patients after a nontraumatic subarachnoid hemorrhage, and either UFH or LMWH in other patients with intracerebral hemorrhage or patients with neurosurgical trauma. The AAST [7], on the other hand, notes that even though LMWH and UFH have comparable bleeding complications, LMWH results in a lower incidence of PE in trauma neurosurgical patients. Consistent with this, we selected LMWH for our protocol as the primary anticoagulant agent. However, patients with poor renal function, assessed as CrCl<30 mL/minutes, will receive UFH instead.

Another critical aspect of our protocol is the introduction of weight-based dosing. Samuel et al [20] have shown that using 7500 Units of UFH in patients on the neurocritical care service who weigh >100 kg does not lead to increased complications. Similarly, Sebaaly and Covert [33] summarize the literature on dose adjustments of LMWH to 30 mg every 8 hours for patients weighing <50 kg or having a BMI of <18 years, reporting comparable complications between higher doses and lower doses of LMWH. The AAST also recommends weight-based dosing for LMWH. Although our study design does not randomize patients, it will allow us to demonstrate the practical challenges of implementing a department-wide VTE prophylaxis protocol in reducing VTE incidence and associated morbidity and mortality.

It is further important to emphasize that VTE cPpx is often used in addition to and not instead of mPpx. Although there is evidence suggesting cPpx may be more effective in reducing the risk of VTE [15,16], all of our patients receive mPpx during their admission unless contraindicated. Consequently, our QI project is not intended to assess the significance of mPpx but rather to assess whether a standardized cPpx protocol may contribute to reducing the overall incidence of VTE and DVT in our patient population.

It is important to consider that a subset of patients may already be on a therapeutic dose of anticoagulation or antiplatelet medications for a history of DVT or PE before hospitalization. Such medications are typically held the evening before a neurosurgical procedure, or in cases of emergency surgery, may be reversed on an individual patient basis. Postoperatively therapeutic dose of anticoagulation or antiplatelet medication may be restarted in these patients. Such patients also continue their regular dose upon discharge. We do not provide a prescription for mechanical VTE prophylaxis other than early mobilization with physical therapy.

### Limitations

As this is a nonrandomized pre-post QI design, the project is susceptible to selection bias and performance bias. Examples of such biases include changes in staffing patterns or seasonal admission trends, which may influence VTE rates. We acknowledge this limitation and address it through stratified subgroup analyses and logistic regression to adjust for known confounders. In addition, although we use multivariable regression to control for common risk factors (BMI, malignancy, immobility, and surgery type), unmeasured, or residual confounding may still influence outcomes. We recognize this as a limitation in attributing causality to the intervention. Finally, there is potential for missing or incomplete documentation in retrospective chart review. We aim to address this through predefined rules for data exclusion and sensitivity analysis, as described in the Methods section.

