## Methods

### Overview

This project is well aligned with the Institute of Medicine’s 6 domains of quality health care and was designed according to the Institute for Healthcare Improvement steps to a good QI project [22]. It aims to avoid harm to patients while being effective in providing prophylaxis according to a risk-based approach. Specifically, the adaptive design assessing outcomes and process measures and implementing incremental change on a quarterly basis ensure the safety of this QI project. Our protocol follows the Agency for Healthcare Research 2017 guidelines to ensure patient safety while implementing this protocol [23]. This quality improvement project has been designed and reported in accordance with the SQUIRE 2.0 (Standards for Quality Improvement Reporting Excellence) guidelines. SQUIRE is the most appropriate framework for reporting system-level interventions aimed at improving health care quality, safety, and outcomes. This manuscript addresses all relevant SQUIRE elements [24]. Further, this project is patient-centered and aims to ensure equitable care for patients by consistently including all eligible individuals in the protocol without discriminating based on demographics. Finally, it is a timely and efficient protocol, reducing inconsistent application of variable guidelines and thus potentially avoiding supplies and staff waste. The assessment of the impact of this protocol on VTE incidence is at 12 and 24 months post implementation, with interim analyses every 3 months to ensure continuous quality improvement. The goal is a 50% decrease in the overall VTE incidence in patients undergoing neurosurgery from 2.5% to 1.25%, with a greater decrease in incidence of VTE among patients undergoing neurosurgical procedures for malignant pathology (cranial or spine). Targeting a reduction to 1.25% represents an achievable improvement that aligns with outcomes seen in successful QI initiatives with standardized protocols [25-27]. For example, the Mercy Hospital Springfield Neurosurgery VTE quality improvement initiative found that VTE occurrence rates in neurosurgery decreased from 3.97% at the time of protocol initiation to 0.72% in January 2020 [26]. All patients admitted to the neurosurgery service for postoperative care will be managed according to the new protocol after the implementation date. The incidence of VTE among patients admitted during the previous 12 months will serve as a control.

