## Results

The desired timeframe for implementing the Neurosurgery VTE prophylaxis protocol is within 6 months of QI project approval, with 1 month of “adaptation time.” Adaptation time is defined as the time between training the staff involved in the project and starting the timeline for outcomes assessment. Department project approval occurred on February 16, 2023, and the project adaptation time began on August 1, 2023.

Data collection is scheduled for completion in 2024, with analysis expected by March 2025. We anticipate a 50% reduction in VTE incidence (from 2.5% to 1.25%) following implementation of a standardized department-wide cPpx protocol. The primary outcome is the incidence of VTE. To assess whether implementation of the protocol results in a meaningful improvement compared to the standard of care, we will use a pre-post design comparing outcomes in the 12 months before and 12 months after the protocol implementation. We will evaluate differences in VTE rates using chi-square or Fisher exact test to compare the proportion of VTE events pre-implementation versus post-implementation. The justification for the chi-square test is that it is appropriate for large samples with expected counts ≥5. The Fisher exact test will be used as a backup for smaller subgroup comparisons where expected frequencies are low. In order to mitigate confounding, we will use multivariable logistic regression, using VTE occurrence as the dependent variable, with covariates including patient-level and procedural risk factors such as BMI, malignancy, surgery type (cranial vs spine), and immobility. The justification is that regression modeling will help isolate any independent effects of the protocol on VTE rates. To account for continuous secondary outcomes, we will perform stratified subgroup analyses for patients with malignancy, those undergoing cranial versus spine procedures, and those receiving LMWH versus UFH. The justification for this is that we will protect against or identify subgroups that experience differential VTE risk. A stratified analysis will determine if the protocol is equally effective across populations.

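### The regression and subgroups said to address staffing and seasonal shifts contain no staffing or calendar-time term, so secular or staffing change outside the four covariates cannot be told apart from the protocol effect

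*Protocol article*

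**What the plan says.** The comparison is between two single years. Methods, Overview: "The incidence of VTE among patients admitted during the previous 12 months will serve as a control". Results: "we will use a pre-post design comparing outcomes in the 12 months before and 12 months after the protocol implementation". There is no concurrent control group.

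The Limitations section lists the threats to this design: "Examples of such biases include changes in staffing patterns or seasonal admission trends, which may influence VTE rates". It labels them selection and performance bias. The next sentence gives the remedy: "We acknowledge this limitation and address it through stratified subgroup analyses and logistic regression to adjust for known confounders".

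The Results section describes that remedy. The logistic regression has "covariates including patient-level and procedural risk factors such as BMI, malignancy, surgery type (cranial vs spine), and immobility", and Limitations repeats the same four factors. The subgroup work is "stratified subgroup analyses for patients with malignancy, those undergoing cranial versus spine procedures, and those receiving LMWH versus UFH".

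The main test in Results is an unadjusted chi-square or Fisher exact comparison of proportions. The success criterion, also in Results, is a fall of at least half, from 2.5% to 1.25% or lower, again unadjusted.

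**The concern.** The remedy does not match the threat. A change in staffing between the two years, or a VTE rate already drifting before implementation, acts on the period as a whole. Adjusting for a patient's BMI, tumour status, type of surgery and mobility removes only the part of a between-year change that works through those factors. Splitting the data by malignancy, site or agent leaves the same before-versus-after contrast inside every stratum.

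The project intends to offer its result as evidence that a unified protocol is effective, possibly as a basis for guidelines. A department whose rate was falling for other reasons could reach the same conclusion, and the Limitations sentence would lead a reader to think this had been handled.

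**Working it through.** **Threat and remedy side by side**

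| Named threat | Matching covariate (Results, Limitations) | Matching stratum (Results) |
|---|---|---|
| Staffing change | none named | none named |
| Seasonal admission pattern | none named | none named |

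Staffing does appear in Methods, Outcomes, as a process measure, but it is recorded when a VTE is diagnosed. As worded, it exists only for patients with the event and cannot serve as a regression covariate.

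**The plan's own figures.** Introduction, Overview: 8 events in 320 cases, July 2020 to June 2021. 8/320 = 2.50%; half is 1.25%; 0.0125 × 320 = 4 events. These reproduce.

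**Can one control year show a trend?** Assume 8 events spread over 12 months (λ = 8/12 a month). For a log-linear Poisson trend, SE(monthly slope) = 1/√(λ·Σ(t − t̄)²) = 1/√(0.667 × 143) = 0.102. Per year that is 12 × 0.102 = 1.23. The 95% interval for the annual rate ratio is exp(±1.96 × 1.23), about 0.09 to 11, which is uninformative. With three such years, Σ(t − t̄)² = 3,885, the annual SE is 0.236 and the interval is about 0.63 to 1.59.

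**How often would background change alone meet the target?** Assume 320 post-year cases, a starting rate of 2.5% and no protocol effect. Success means X ≤ 4, with X ~ Binomial(320, 0.025 × (1 − fall)).

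| Assumed background fall | True post-year rate | P(X ≤ 4) |
|---|---|---|
| 0% | 2.50% | 9.7% |
| 10% | 2.25% | 15.2% |
| 20% | 2.00% | 23.2% |

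**Does seasonality bias the contrast?** In a 24-month Poisson series (8 events before, 4 after), SE(log rate ratio) = √(1/8 + 1/4) = 0.612. Adding sine and cosine season terms leaves it at 0.612, because two full years have the same seasonal make-up. The balance is lost if the windows are unequal. Adaptation time began on August 1, 2023, and collection is scheduled to end by December 2024. Counting from August, September or November 2023 to December 2024 gives 17, 16 or 14 months.

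**What would a calendar-time term do?** SE of the log rate ratio for the protocol, from the Poisson information matrix on monthly data with 8 events per pre-year and 4 post-year:

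| Data | Step only | Step plus linear time |
|---|---|---|
| One pre-year | 0.61 | 1.18 |
| Three pre-years | 0.54 | 0.71 |

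Around a rate ratio of 0.5, the 95% interval is 0.5 × exp(±1.96 × SE). It is about 0.15 to 1.66 for the simple one-year contrast, 0.05 to 5.0 with a time term on the same two years, and 0.12 to 2.0 with a time term on three pre-years.

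**The case against.** The plan is more candid than the one sentence suggests. Limitations says that unmeasured or residual confounding may remain and that this limits causal attribution. Methods, Selecting Change, plans a monthly run chart and says that process and balancing measures will be assessed as confounders. The covariate list is open-ended, in a condensed article whose analysis plan is not shown. An uncontrolled before-after comparison is a disclosed and ordinary choice for a departmental quality project.

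Much of this stands, but it does not repair the sentence. The causality caveat is general and does not withdraw the claim that staffing and seasonal shifts are addressed. The run chart has no stated pre-implementation period or trend rule and feeds neither the test nor the success criterion. Lengthening the covariate list would not help on the present two years, as the SE of 1.18 shows.

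Three stronger readings are tempting and not supported:

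- A reader might infer that every background change is credited to the protocol. Case-mix shifts acting through the four covariates are adjusted for in the regression, though not in the main test.
- A reader might infer that seasonality biases the result. Two complete, matched years balance a stable seasonal pattern.
- A reader might infer that a plausible drift would reach the target by itself. A 20% yearly fall gives 2.5% × 0.8^3.16 = 1.24% only over the roughly 3.2 years from the middle of the 2020-21 benchmark year to the middle of the post-year (assumed to start about September 2023). Against the control that the plan defines, the preceding 12 months, one year's fall of 20% gives 2.0%. The documents report no trend at all. Which baseline applies is a separate matter to reconcile.

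**Conclusion.** The point holds in a limited form. Limitations claims a safeguard that the named analyses do not provide. Secular or staffing change outside BMI, malignancy, surgery type and immobility is inseparable from the protocol effect in a one-year-versus-one-year comparison, and the unadjusted test and criterion would count it as benefit. Background falls of 10% and 20% raise the chance of meeting the target without any protocol effect from about 10% to 15% and 23%. This rests on 320 post-year cases, a 2.5% starting rate and falls chosen for illustration.

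Earlier years would make a prior trend visible but would not yield a precise trend-adjusted effect. A reader might expect extra years to sharpen the estimate, since the SE of the simple contrast falls from 0.61 to 0.54. That gain assumes no trend; with the time term the SE is 0.71. A trend model is therefore not a suitable main analysis at 4 to 8 events a year.

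**What to change.** 1. In Limitations, state that the stratified analyses and the patient-level regression do not address secular or staffing trends.
2. Beside the 12-versus-12-month comparison, report VTE rates by year for the complete 12-month blocks from July 2020 to implementation, using the same case definition and data source throughout.
3. State in advance that a fall already under way before implementation will not be attributed to the protocol.
4. Keep both comparison windows at a full 12 months covering the same calendar months, so that a stable seasonal pattern stays balanced.
5. Optionally, fit a calendar-time term to the multi-year data as a sensitivity analysis only, and report its interval so that the imprecision is visible.

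The cost is retrospective registry or chart queries for about two more years, a small amount of text, and a more cautious conclusion. Patient care is unaffected. If the earlier years cannot be obtained on the same definition, the correction to Limitations should still be made.

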## Appendix

Multimedia Appendix 1 Guidelines summary.

## Abbreviations

AANS: American Association of Neurological Surgeons
AAST: American Association for the Surgery of Trauma
ACCP: American College of Chest Physicians
ACS: American College of Surgery
CNS: Congress of Neurological Surgeons
cPpx: pharmacologic prophylaxis, chemoprophylaxis
CrCl: creatinine clearance
DVT: deep vein thrombosis
HHS: US Department of Health and Human Services
HIPAA: Health Insurance Portability and Accountability Act
ICU: intensive care unit
IVC: inferior vena cava
IRB: institutional review board
LMWH: low molecular weight heparin
mPpx: mechanical prophylaxis
NASS: North American Spine Society
NCC: Neuro Critical Care
NSQIP: National Surgical Quality Improvement Program
OHRP: Office for Human Research Protections
OR: odds ratio
PE: pulmonary embolism
QI: quality improvement
RR: relative rate
SCD: sequential compression device
SCI: spinal cord injury
SQUIRE: Standards for Quality Improvement Reporting Excellence
TBI: traumatic brain injury
UFH: unfractionated heparin
VTE: venous thromboembolism
